**Fig. 1 Fig1:**
[figure not shown]
IPOS trial—schedule of enrolment, interventions, and assessments

#### Between weeks 2 and 12 (up to the end of the 3rd month) (only for the intervention arm)

Once a week text messages and/or videos on diet and physical exercise to re-in force the intervention.

Once a month telephonic contact to assess compliance with diet/exercise with the participant.

#### Week 13– (session 2) (only for the intervention arm)

In person to check compliance for diet and physical exercise, check weight and anthropometric parameters and as the pregnancy status of the participants. An ultrasound will be performed before initiating ovulation induction.

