## Method and design

### Aim of the study

The overall aim of the study is to evaluate the efficacy of individualized lifestyle intervention compared to the usual care in PCOS women who wish to conceive. We hypothesized that individualized lifestyle intervention improves fertility outcomes in PCOS women who wish to conceive when compared to the usual care. To test the hypothesis, we plan to randomize PCOS women into two groups: group A will receive the intervention which will consist of individualized advice on diet and physical exercise along with a telephonic reminder system and follow-up visits, and group B (control) will receive one-time advice on diet and physical exercise. Both groups will receive up to three cycles of ovulation induction with letrozole after 3 months of randomization during the 6-month treatment period.

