### Control

Usual care, which is the medical advice/fertility treatment as per unit protocol for those seeking fertility treatment and one time referral to the dietician for dietary advice and exercise by the physiotherapist in the fertility clinic. There will be no planned follow-up for compliance for the lifestyle intervention in the control arm. The control also will receive the fertility treatment after 3 months following randomization if they do not conceive as per unit protocol. The participant will be reviewed after 6 months to measure the anthropometric and reproductive outcomes at the department of reproductive medicine and surgery/gynaecology outpatient clinic. This visit will be combined with any medical treatment-related appointment to avoid multiple visits to the hospital. As mentioned, the participant in the control arm also will receive medical treatment as per unit protocol 3 months post-randomization if she does not conceive.

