### Medical treatment 3 months post-randomization for intervention and control arm

These will be as per standard infertility guidelines starting with letrozole. Ovarian induction may be followed with timed intercourse or IUI (combined male factors such as sexual dysfunction) as per the participant’s profile. The treatment will be given for up to 3 cycles depending on the unit policy, while the lifestyle intervention follow-up will continue in the interventional arm over the next 3 months, to be completed for 6 months.

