#### Week 26– (session 3) (for both the intervention and control arms)

In person check anthropometry and blood tests (hormones and metabolic parameters) and TVS. The following blood tests will be repeated at 6 months: AMH, serum testosterone, SHBG, serum insulin (fasting and 2 h post-meal), blood sugar (fasting and 2 h post-prandial), fasting lipid profile, glycosylated haemoglobin (HbA1C), SGPT, uric acid and serum adiponectin.

Compliance with dietary intake and physical exercise will be assessed for participants in the intervention and control arms using 24 h diet recall and GPAQ tool.

Medical treatment for infertility can be commenced after 12 weeks on post-randomization in case the participant does not conceive. The lifestyle intervention shall stop at 6 months when a final follow-up on anthropometry, metabolic, hormonal and ultrasound will be done in women from both arms. For those who conceive within 6 months post-randomization, the follow-up will extend until delivery/end of pregnancy for recording obstetrics and neonatal outcomes.

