### Primary outcome

The primary outcome for the trial will be the live birth following conception during the intervention period (time frame: 0 to 16 months post-randomization for participants who conceive within 6 months following randomization). A live birth is defined as the delivery of a live foetus after 20 weeks of gestation [23]. The twins and higher births will be considered as a single live birth event. The denominator for primary analysis will be per woman.

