We plan to adjust the results for the following covariates: (i) number of letrozole cycles. Logistic regression analysis will be used to adjust the covariates effectively the adjusted effect size will be presented as an odds ratio (95% CI) for binary outcomes. All the analyses will be performed using STATA/IC 16.0.

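### Time to pregnancy stops when a pregnancy is documented, but the week-13 pregnancy check is scheduled in the intervention arm only, so the same conception can be dated earlier in that arm

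*Protocol article*

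**What the plan says.** All references are to the protocol article.

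- **Secondary outcomes, time to pregnancy.** The clock starts at randomization and stops on the day pregnancy is documented. The time frame is 0 to 8 months for women who conceive in the first 6 months, so the plan itself allows documentation to trail conception.
- **Week 13 session.** The heading limits it: "session 2) (only for the intervention arm". It is in person, includes a check of pregnancy status, and adds: "An ultrasound will be performed before initiating ovulation induction".
- **Weeks 2–12 and 14–25.** Monthly telephone contact to assess compliance, again in the intervention arm only.
- **Control.** "The participant will be reviewed after 6 months to measure the anthropometric and reproductive outcomes". The week-26 session covers both arms, and Table 1 lists only a 6-month assessment for controls.
- **Letrozole.** "Both groups will receive up to three cycles of ovulation induction with letrozole after 3 months of randomization during the 6-month treatment period" (Aim of the study). The week-26 section adds: "Medical treatment for infertility can be commenced after 12 weeks on post-randomization in case the participant does not conceive". The medical treatment section, headed for both arms, says: "The treatment will be given for up to 3 cycles depending on the unit policy".
- **Primary outcome.** "live birth following conception during the intervention period", limited to conceptions within 6 months of randomization.
- **Blinding.** The trial is open-label. The plan relies on most outcomes being objective and concedes that performance bias remains possible.

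**The concern.** Whether a woman is pregnant is objective. The day on which someone records it depends on when someone looks. If one arm has an additional scheduled look at week 13, an event date defined by documentation will tend to be earlier in that arm even when the conception dates are identical. Neither participants nor staff are blinded, so nothing in the design offsets this.

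At stake is the interpretation of time to pregnancy. A shorter time in the intervention arm could reflect faster conception or merely earlier detection, and the definition as written cannot separate the two. The visits belong to the lifestyle package, but earlier detection is not a fertility benefit of that package.

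**Working it through.** The plan gives no figure for this point, so the check sets the schedule beside the outcome definition.

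**1. Scheduled pregnancy ascertainment by arm, as the text describes it**

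| Time | Intervention | Control |
|---|---|---|
| Weeks 0–1 | pregnancy status recorded | pregnancy status recorded |
| Week 13 | in-person pregnancy check; ultrasound before induction | none described |
| Before first letrozole cycle (from 12 weeks) | as above | implied, because letrozole is only for women who have not conceived; date and content not stated |
| Week 26 | in-person review | in-person review, including reproductive outcomes |

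**2. Which conceptions are exposed.** Mainly those in roughly the first 3 months, before letrozole. An intervention-arm woman with a detectable pregnancy is found by week 13 at the latest if she attends. A control who has conceived needs no letrozole. Her pregnancy is recorded when she reports it, when she attends for treatment, or at the 6-month review. After week 13 the scheduled in-person checks described are the same in both arms.

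**3. Ceiling on the scheduled gap.** Week 13 to week 26 is (26 − 13) × 7 = 91 days. If a share s of control pregnancies is documented d days later than it would have been in the intervention arm, the control mean rises by s × d. At the ceiling, each 10% of control pregnancies adds 0.10 × 91 = 9.1 days. Neither s nor the typical d is in the documents, and d may be close to zero for most women.

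**4. Direction.** An extra check adds an opportunity for earlier documentation, so the expected direction favours the intervention. There is an exception. A control who attends for letrozole at exactly 12 weeks would be checked (13 − 12) × 7 = 7 days before the intervention arm's visit.

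**5. Does this reach live birth through letrozole timing?** This can only be illustrated.

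- Window to week 26: 98 days from week 12, 91 days from week 13.
- Assume ovulation 14 days before cycle end. The third ovulation then falls on day 3c − 14, which is day 70, 76 or 91 for c = 28, 30 or 35 days. Slack is 28, 22 or 7 days from week 12, and 21, 15 or 0 days from week 13.
- Assume the 30% control rate is spread evenly over five cycles: p = 1 − 0.7^(1/5) = 0.0689. Three cycles give 0.193 and two give 0.133, a loss of 0.060. Spread over three cycles: p = 1 − 0.7^(1/3) = 0.1121. Three cycles give 0.300 and two give 0.212, a loss of 0.088.
- Assume 10% of one arm loses the third cycle and nobody in the other does. The difference shifts by 0.10 × 0.060 = 0.006 or 0.10 × 0.088 = 0.009.
- With 600 per arm and SE = √[p₁(1 − p₁)/600 + p₂(1 − p₂)/600] = 0.02263 or 0.02634, the two-sided rejection rate with no true effect is about 0.045 + 0.013 = 0.058 or 0.052 + 0.011 = 0.063, against 0.05.

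The 10% one-arm loss has no source in the documents.

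**The case against.** The strongest reply is that the week-13 heading sits in the section on delivering the lifestyle intervention, while fertility treatment has its own section covering both arms. The Control section rules out planned follow-up for lifestyle compliance, not fertility contact, and it expects treatment appointments. Controls must be found not pregnant before letrozole, so some check near 3 months is implied. The dropout criteria mention visits at 3 and 6 months without naming an arm, and newly detected prediabetics have HbA1c at 3 months. The schedule figure (Fig. 1) was not available to this review and might show a control contact.

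Much of this stands. A control contact near 3 months is likely for women who go on to letrozole, which keeps the typical gap well below its ceiling. It does not remove the point. Women who conceive before letrozole have no reason to attend for it, and an implied check with no stated date is not the same as a scheduled one. If Fig. 1 does show a control visit, the week-13 heading needs correcting.

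A reader might infer something stronger: that letrozole starts at different times in the two arms and so biases live birth. The documents do not support that. Both arms share the drug, the three-cycle cap, the trigger, the earliest start and the 6-month limit. Unit policy acts on both arms within a site, and randomization is stratified by site. A latest start date is detail that an article may leave to the full protocol. A difference in start is possible but not shown.

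Two neighbouring matters are separate and prove nothing here: the differing dropout wording in the Dropout criteria and Table 1, and the planned covariate adjustment ("We plan to adjust the results for the following covariates: (i) number of letrozole cycles").

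**Conclusion.** The point holds for time to pregnancy. Followed as written, the plan can date the same conception earlier in the intervention arm, because the event date is the date of documentation and the week-13 pregnancy check is scheduled in that arm only. The expected direction favours the intervention. The scheduled checks are at most 91 days apart for one woman; the average shift cannot be derived and may be small. This rests on the text alone, without Fig. 1, and on controls having no scheduled check near 3 months beyond what letrozole treatment implies.

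For live birth, neither size nor direction can be derived. Even the illustrative one-arm loss of a third cycle in 10% of women moves the two-sided error only from 5% to about 6%. The primary ITT comparison is not called into question.

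**What to change.** 1. In both arms, define the event date for time to pregnancy as the estimated date of conception, from last menstrual period or early ultrasound dating. Use the same date to decide whether a conception falls inside the 6-month window.
2. State that the pregnancy test and ultrasound before the first letrozole cycle apply to both arms. For controls, use the treatment appointment they need anyway, with no diet or exercise content.
3. Report letrozole start date and number of cycles by arm as a description of treatment received. Leave the ITT comparison unchanged.

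The first change costs almost nothing. The second adds at most one structured fertility contact per control still not pregnant at 3 months (up to 600 women), most of whom are likely to need that appointment for letrozole. The downside is that control care becomes slightly more structured than usual care, and control retention may rise. The sample size is unaffected.

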#### Weeks 14–25 (only for the intervention arm)

Once a week text messages and/or videos on diet and exercise to re-in force the intervention.

Once a month in telephonic contact to assess compliance for diet/exercise with the participant.

#### Week 26– (session 3) (for both the intervention and control arms)

In person check anthropometry and blood tests (hormones and metabolic parameters) and TVS. The following blood tests will be repeated at 6 months: AMH, serum testosterone, SHBG, serum insulin (fasting and 2 h post-meal), blood sugar (fasting and 2 h post-prandial), fasting lipid profile, glycosylated haemoglobin (HbA1C), SGPT, uric acid and serum adiponectin.

Compliance with dietary intake and physical exercise will be assessed for participants in the intervention and control arms using 24 h diet recall and GPAQ tool.

Medical treatment for infertility can be commenced after 12 weeks on post-randomization in case the participant does not conceive. The lifestyle intervention shall stop at 6 months when a final follow-up on anthropometry, metabolic, hormonal and ultrasound will be done in women from both arms. For those who conceive within 6 months post-randomization, the follow-up will extend until delivery/end of pregnancy for recording obstetrics and neonatal outcomes.

### Primary outcome

The primary outcome for the trial will be the live birth following conception during the intervention period (time frame: 0 to 16 months post-randomization for participants who conceive within 6 months following randomization). A live birth is defined as the delivery of a live foetus after 20 weeks of gestation [23]. The twins and higher births will be considered as a single live birth event. The denominator for primary analysis will be per woman.

### Secondary outcomes

There will be several secondary outcomes which will measure clinical, endocrinological and quality of life parameters and are listed below:(i)Clinical pregnancy rate (time frame: 0 to 9 months post-randomization for participants who conceive within 6 months following randomization): ultrasound evidence of gestational sac or definitive clinical evidence of pregnancy. An ectopic pregnancy will also be considered a clinical pregnancy [24].(ii)Ongoing pregnancy rate (time frame: 0 to 9 months post-randomization for participants who conceive within 6 months following randomization): a viable intrauterine pregnancy as documented by ultrasound after 12 completed weeks of gestation.(iii)Miscarriage rate (time frame: 0 to 12 months post-randomization for participants who conceive within 6 months following randomization): miscarriage is defined as a spontaneous loss of pregnancy before 20 completed weeks of gestational age [23].(iv)Ectopic pregnancy rate (time frame: 0 to 9 months post-randomization for participants who conceive within 6 months following randomization): ectopic pregnancy is defined as pregnancy outside the uterus as diagnosed by ultrasound, surgically or by histopathology [24].(v)Stillbirth: defined as the death of a foetus prior to the complete expulsion or extraction from its mother after 20 completed weeks of gestational age [23].(vi)Time to pregnancy (time frame: 0 to 8 months post-randomization for participants who conceive within 6 months following randomization): from randomization to the documentation of pregnancy (calculated in days).(vii)Positive pregnancy rate (time frame: 0 to 7 months for participants who conceive within 6 months following randomization): defined as positive urine pregnancy test or serum beta human chorionic gonadotrophin (hCG) > 5 IU/ml.(viii)Mean weight loss (time frame: 6 months post-randomization): difference between baseline and follow-up at 6 months).(ix)Improvement in menstrual regularity (time frame: 6 months post-randomization): (according to the International Federation of Gynecology and Obstetrics (FIGO) 2018 guidelines variation of the cycle to be called regular is 7–9 days depending on age. Age 18–25 years ≤ 9 days; age 26–41 years ≤ 7 days is regular); proportion of women in whom regularization of the menstrual cycle is recorded by a total number of women in whom menstrual regularity is recorded.(x)Differences in anthropometric parameters (time frame: 6 months post-randomization) (waist circumference, hip circumference, neck circumference, waist hip ratio, waist height ratio and wrist circumference) at the end of the trial period.(xi)Improvement in hormonal and metabolic parameters (time frame: 6 months post-randomization) [biochemical markers such as lipid profile and glycaemic parameters, visceral adiposity index (VAI) and lipid accumulation product (LAP)] over the baseline.(xii)Quality of life (PCOS specific) assessment (time frame: 6 months post-randomization) [22].(xiii)Pregnancy-related complications (time frame: 0–17 months post-randomization for participants who conceive within 6 months following randomization) (GDM, PIH, preterm birth): obstetric outcomes—gestational diabetes, hypertensive disorder of pregnancy, preterm delivery (< 37 weeks), very preterm birth (< 32 weeks), low birth weight (< 2500 g) or high birth weight (> 4000 g)

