### Inclusion and exclusion

Women attending the fertility clinic will be screened for eligibility. The inclusion criteria will be (i) women aged between 19 and 37 years who have been diagnosed as PCOS by the Rotterdam criteria and wishing to conceive, (ii) body mass index (BMI) ≥ 23 kg/m^2^ but ≤ 35 kg/m^2^ and (iii) duration of infertility ≤ 3 years. The exclusion criteria will be as follows: (i) women planning to take medical treatment at hometown and not available for follow-up period (6 months); (ii) does not have a mobile phone in the house; (iii) pregnancy; (iv) late-onset congenital adrenal hyperplasia (CAH) and androgen secreting tumours; (v) diabetes mellitus, uncontrolled hypothyroidism (TSH > 10 IU/ml), hyperprolactinemia (> 70 ng/ml), bronchial asthma, chronic kidney and liver disease; (vi) prediabetic on metformin or insulin sensitizers or other anti-diabetic medicines; (vii) inflammatory arthritis or any lower limb pathology which precludes exercise; (viii) gastro-intestinal conditions (e.g. ulcerative colitis, Crohn’s disease, coeliac disease) which require special dietary advise; (ix) on anti-psychiatric medications; (x) undiagnosed uterine bleeding; (xi) medical conditions which are contraindications for pregnancy; (xii) previous history of receiving > 6 ovulation induction cycles with letrozole or laparoscopic ovarian drilling; (xiii) previous history of bariatric surgery or planning other strategies for weight loss beyond the trial intervention including but not limited to Fad diets, intra gastric procedures or on weight loss medication; and (xiv) other known causes of infertility which are indications for assisted reproductive technology (ART) treatment, namely severe endometriosis, severe male factor infertility, male partner with azoospermia and documented severe tubal pathology.

Newly detected prediabetics will be included only if they are willing for an initial trial of lifestyle intervention for glycaemic control. We will repeat glycosylated haemoglobin (HbA1c) at 3 months interval, post-randomization, to assess the glycaemic control. If the Hb1Ac is ≥ 6.5%, then initiation of metformin will be considered, and the participant will be followed up as per protocol but will not be considered for per protocol analysis.

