### Sequence generation and allocation concealment

Once eligibility is confirmed, web-based randomization will be initiated in the presence of the trial staff. The randomization will be done using PHP as the frontend and MySQL as the backend database. Block randomization stratified for the site and BMI (≥ 23–27 kg/m^2^ and > 27 to ≤ 35 kg/m^2^) will be performed. The randomization will be done in a 1:1 ratio to the intervention or the control arm. The trial staff from each site will enter the participant information following which a randomization number will generated and assigned if they fulfil the eligibility criteria. The random number and the allotted arm details will be provided to the trial staff by an authorized person in each site. The allocation will be concealed until the point of randomization. The allotted intervention will be informed to the clinical team as well as the trial staff, and the trial number will be noted.

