### Sample size calculation

No previous data is available on live birth following individualized lifestyle intervention in PCOS women who wish to conceive. From previous study performed in one of the trial sites, the live birth rate following usual care which consisted of one-time lifestyle advise and ovulation induction with Letrozole for up to five treatment cycles, was reported as 30% [25]. Due to uncertainty about the likely event rate (live birth rate) in the intervention arm, it was assumed that to convince the clinicians and patients to adopt a change in practice, a modest improvement of 10% in live birth would be required.

For alpha error set at 0.05 and power being 90%, to detect a clinically relevant difference of 10% in the live birth rate following individualized lifestyle intervention, the calculated sample size will be 473 in each arm (total sample size 946). Assuming an attrition of 20%, the total sample size was 1183. We rounded off the total sample size to 1200 with 600 in each arm. With 5 centres participating in the study each site shall recruit 240 subjects each.

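### The hCG cut-off for a positive pregnancy and the TSH cut-off for exclusion are both written in IU/ml, a unit that can hardly be intended for either; the sponsor should confirm and correct both.

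*Protocol article*

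**What the plan says.** Two decision limits in the protocol article are given in IU/ml.

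- **Secondary outcomes, item (vii), positive pregnancy rate:** "defined as positive urine pregnancy test or serum beta human chorionic gonadotrophin (hCG) > 5 IU/ml". The two tests are alternatives, and the time frame is 0 to 7 months for women who conceive within 6 months of randomization.
- **Inclusion and exclusion, exclusion (v):** "uncontrolled hypothyroidism (TSH > 10 IU/ml), hyperprolactinemia (> 70 ng/ml", within a list of medical conditions. The prolactin limit next to TSH is in ng/ml.

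No other section restates either limit or gives it in another unit. The article does not say in which unit the laboratory reports hCG or TSH.

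Two related statements bear on use. Clinical pregnancy, item (i), rests on ultrasound or definitive clinical evidence and has a time frame of 0 to 9 months. Under Sequence generation and allocation concealment, trial staff enter participant information into a web system, which assigns a randomization number if the eligibility criteria are fulfilled.

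**The concern.** Both limits are working rules: one decides whether an outcome has occurred, the other whether a woman may enter the trial. Someone who builds a CRF field, a range check or an eligibility screen from the article would take the number and the unit together.

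For hCG, item (vii) has the shorter time frame and needs no ultrasound, so it is evidently meant to record pregnancy earlier than item (i). A serum limit of several thousand mIU/ml works against that. It also lets the two halves of the definition disagree, since a woman could be positive by urine and negative by serum at the same time. The article does not say which test a site should use, so on a literal reading the count would depend partly on the test chosen.

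For TSH, a limit that no result can exceed adds nothing to the criterion. An automated check that used it would pass every woman.

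**Working it through.** **Inputs from the article**

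- hCG limit: 5 IU/ml (Secondary outcomes, vii).
- TSH limit: 10 IU/ml (Inclusion and exclusion, v).

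**Assumption, not in the article:** hCG is ordinarily reported in mIU/ml, which equals IU/L, and TSH in µIU/ml, which equals mIU/L.

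**Conversion:** 1 IU/ml = 1,000 mIU/ml = 1,000 IU/L = 1,000,000 µIU/ml = 1,000,000 mIU/L.

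**hCG**

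- 5 IU/ml × 1,000 = 5,000 mIU/ml (5,000 IU/L).
- Ratio to the same number in mIU/ml: 5,000 / 5 = 1,000.
- Illustration: a serum result of 200 mIU/ml is 200 / 1,000 = 0.2 IU/ml, which is below 5 IU/ml. The serum test would be negative under the written rule. The woman would still count if a urine test were positive.

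**TSH**

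- 10 IU/ml × 1,000,000 = 10,000,000 µIU/ml (10,000,000 mIU/L).
- Ratio to the same number in mIU/L: 10,000,000 / 10 = 1,000,000.

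**How far the factors depend on the assumption**

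| Unit intended | hCG: written limit relative to intended | TSH: written limit relative to intended |
|---|---|---|
| IU/ml, as written | 1 | 1 |
| mIU/ml (IU/L) | 1,000 | 1,000 |
| µIU/ml (mIU/L) | 1,000,000 | 1,000,000 |

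Under the assumption, the middle row applies to hCG and the last row to TSH.

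**Effect on the design.** The article's sample size can be reproduced, and neither threshold enters it. The inputs are a control rate that "was reported as 30"% and an improvement of 10 percentage points, with alpha 0.05 (taken as two-sided) and power 90%. With unpooled variance:

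n per arm = (z for alpha + z for power)² × [p1(1 − p1) + p2(1 − p2)] / (p2 − p1)²

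= (1.960 + 1.282)² × (0.30 × 0.70 + 0.40 × 0.60) / 0.10² = 472.8, rounded up to 473.

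The total is 2 × 473 = 946, and 946 / 0.80 = 1,182.5, rounded up to 1,183. Both agree with the article. The primary outcome, live birth, does not use hCG or TSH.

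**The case against.** The strongest reply is that this is a slip in a unit prefix that gives itself away. A laboratory report carries its own unit, and staff comparing a result with 5 or 10 would probably read through the error. The CRF and the web check are not shown, so nothing establishes that they carry the wrong unit. For TSH, a micro sign might have been lost when the PDF was read. Other special characters, such as ≥ and ≤, survive, so this is only a possibility, and it would not explain the hCG unit. These points justify treating the matter as minor. They do not make the printed definitions right.

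Three stronger readings are tempting, and the article does not support them.

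- **Bias between arms.** A reader might infer that one arm would record fewer early pregnancies. Randomization is stratified by site, so a site's preference for serum or urine tests falls on both arms. The intervention arm has an extra visit at week 13 at which pregnancy status is checked, but the article does not name the test, and nothing links test type to arm.
- **A disabled safety rule.** The article lists the criterion only as an exclusion and does not call it a safety rule. It also names uncontrolled hypothyroidism, with the number in parentheses, so a clinician can still apply it.
- **A broken outcome.** A literal reading loses only women tested by serum alone whose result never exceeds the written limit within the time frame. A pregnancy seen on ultrasound is still counted under item (i). Time to pregnancy, item (vi), runs to the documentation of pregnancy without citing the hCG limit, so it would be touched only if sites used item (vii) as that documentation.

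**Conclusion.** The point stands as a minor correction. Two operative limits are wrong as printed if the ordinary assay units were meant: hCG by a factor of 1,000 and TSH by a factor of 1,000,000. The conversions are certain. The factors rest on the assumed units, and the statement that the TSH limit would exclude nobody rests on the further assumption that no patient has a TSH near 10,000,000 mIU/L. Confidence is slightly lower for TSH because of the possible lost character.

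The consequence is confined to one secondary outcome and one eligibility limit. How many pregnancies or enrolments could be affected cannot be estimated, because the article does not say how often serum is used without urine or how the checks are programmed. The documents also do not establish which unit was intended. A reader might conclude that a particular corrected cut-off follows, but that is for the sponsor to confirm.

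**What to change.** - The sponsor confirms the intended number and unit for both thresholds against the source protocol.
- Secondary outcome (vii) and exclusion (v) are corrected to the unit the laboratory reports.
- The CRF, the database range checks and the web eligibility check are compared with the corrected text, so that all use the same units. If any already used the printed units, the affected records are re-examined.

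The cost is a unit correction in two places and a check of existing forms. It needs no additional patients, tests or redesign, and no change to the analysis.
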